A systematic review of mental health and psychosocial support for children (7-18 years old) in humanitarian settings identified knowledge gaps regarding effective strategies to reduce depression and anxiety [3]. Strategies in Uganda included sports for development, which only resulted in positive effects for boys [13], and a creative play group, which only resulted in positive effects for girls [14]. A 2018 cross-sectional survey with urban refugee and displaced youth (N=445) aged 16-24 years in Kampala, Uganda, found that three-quarters (74%) of adolescent girls and young women, and nearly half (49%) of adolescent boys and young men reported depressive symptoms [4]. These alarming statistics highlight the need for concrete solutions developed with and for urban refugee youth to alleviate this distress and risk of depression. In July 2020, Uganda opened its borders to receive more refugees from the Democratic Republic of the Congo (DRC) in the midst of the COVID-19 pandemic [15]. While mental health risks may be heightened during pandemics such as COVID-19 [16], researchers identified a chronically high prevalence of depression among urban refugee youth in Kampala both before (27.5%) and after (28.9%) declaration of the pandemic in March 2020 [17], signaling the urgent need to address chronic depression among this population.

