### Outcomes

#### Primary Outcome

The primary outcome measured in this trial is *depression*, which will be measured using the Patient Health Questionnaire-9 [56].

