### Sample Size and Power Analysis

The study aims to include 330 participants, with 110 per study arm. Cluster sizes of 90 per group (n=270) are required to have 80% power (*P*<.05) to detect a difference of ~3 points in mean depression score (moderate effect size) at a level of significance of α=.05, assuming an intraclass correlation of 0.01 and SD of 7. With 10% attrition, 297 participants (99 per cluster) are required. Computations were performed using RStudio version 3.3.0, based on formulae for multiple comparisons of proportions and adjusted for design effect [58].

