### Data Analysis Plan

Analysis and reporting for the cRCT (Phase 2) will be conducted in accordance with CONSORT (Consolidated Standards of Reporting Trials) guidelines [59] (Multimedia Appendix 1). The analyst will be blinded to group allocation. A flow diagram will be used to illustrate patient flow (screening, randomization, allocation, follow-up). Baseline data will be reported for all three groups and summarized as mean (SD) or median (IQR) for continuous variables, and as counts and number (%) for categorical variables. The primary analysis will be intention-to-treat analysis (data from participants will be analyzed according to their allocation, irrespective of whether they actually received that intervention).

We will perform multivariable regression analyses, adjusting for the outcome measure at baseline and stratification variables. For the primary analysis to assess differences among the three intervention conditions on the outcomes, indicator variables will include intervention assignment and a vector of baseline covariates (eg, sociodemographics). Analyses will adjust for multiple comparisons across the three intervention conditions using the Fisher protected least-significant difference test, first assessing differences between intervention groups and, if the Omnibus *F* test is significant, subsequently calculating pairwise comparisons.

Between-group comparisons will be performed using multilevel mixed-effects logistic or linear regression models (to account for clustering) depending on which outcome is being evaluated. For these models, the intervention group will be entered as a fixed effect. The significance level will be set at α=.05. The results will be expressed as odds ratios or mean differences, as appropriate, accompanied by 95% CIs and *P* values. We will perform an adjusted analysis for the primary outcomes to investigate the role of various covariates on the relative effect. Covariates (eg, age) will be entered as a block. We will explore gender differences in primary and secondary intervention outcomes. Given that the outcomes of this study are related to behavior change and the trial is of a short duration with minimal risks, a data monitoring committee was not deemed necessary.

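### The sample-size paragraph uses mean-score inputs but names a formula for proportions, and the article never says whether the primary PHQ-9 result is a mean difference or an odds ratio

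*Protocol article*

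**What the plan says.** Four places in the protocol article bear on the metric of the primary outcome.

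- **Primary Outcome.** The outcome is depression, "which will be measured using the Patient Health Questionnaire-9". Neither the total score nor a cut-off is mentioned, and no primary time point is chosen between 8 and 16 weeks.
- **Sample Size and Power Analysis, inputs.** The requirement reads "Cluster sizes of 90 per group (n=270) are required to have 80% power". The effect sought is put as "to detect a difference of ~3 points in mean depression score (moderate effect size". Alpha is 0.05. The spread of scores and the clustering enter by "assuming an intraclass correlation of 0.01 and SD of 7".
- **Sample Size and Power Analysis, method.** The last sentence says the computations were "based on formulae for multiple comparisons of proportions and adjusted for design effect".
- **Data Analysis Plan.** Between-arm comparisons use "multilevel mixed-effects logistic or linear regression models (to account for clustering) depending on which outcome is being evaluated". Results are to be given as odds ratios or mean differences as appropriate. No outcome is assigned to either model. The same section puts an omnibus F test before the pairwise comparisons.

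The Introduction states the primary objective only as reducing depression.

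**The concern.** The inputs and the named method within one paragraph are incompatible. A formula for proportions needs a control rate and a target rate, and the article gives neither. A mean difference and an SD can feed only a formula for means. A reader cannot tell which calculation produced 90 per group, and the rest of the article does not say which summary of the PHQ-9 is primary.

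The metric decides the effect measure, the model and the power for the only primary outcome. A total-score comparison and an above-cut-off comparison answer different questions, and the second has clearly less power for the same underlying shift. Leaving the choice unrecorded also leaves room for doubt, when results appear, about whether the reported metric was the planned one.

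**Working it through.** **Inputs from Sample Size and Power Analysis:** difference 3 points, SD 7, α = 0.05, power 80%, 90 per group, intraclass correlation 0.01, cluster size 90. Sidedness is not stated, so I take two-sided.

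**Step 1. Reproduce the plan's figure with a formula for means.**
n per arm = 2 × 7² × (1.960 + 0.842)² / 3² = 85.5, so 86 (87 with the t distribution).
Power at 90 per arm = Φ(3 / (7 × √(2/90)) − 1.960) = Φ(2.875 − 1.960) = 0.82.
This is close to the stated 90 and 80%. A difference of 2.93 points gives exactly 90, which agrees with a target of about 3. No design effect has been applied so far.

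**Step 2. Apply the stated design effect.**
1 + (90 − 1) × 0.01 = 1.89.
Size needed = 86 × 1.89 ≈ 163 per arm. This is a lower bound if the extra participants join the same clusters, because cluster size then rises too.
Effective size of 90 = 90 / 1.89 = 47.6, and power = Φ(3 / (7 × √(2/47.6)) − 1.960) = Φ(2.091 − 1.960) = 0.55.
If the cluster were taken as 45 (two settlements sharing an arm of 90), the design effect is 1.44 and power is about 67%. The formula for means times a design effect returns 90 only for clusters of about 5 or 6, which is not the stated size.

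**Step 3. Try a formula for proportions.**
It cannot be run on the stated inputs, because no control rate, target rate or cut-off is given for sizing. Pairs about 17 to 20 percentage points apart would also land near 90 (74% against 54% needs 90; 28.9% against 12% needs 89), but the article states no such target. So the figure of 90 alone does not reveal which formula was run.

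**Step 4. Illustrate what the metric does to power.**
Assumptions: normal scores with common SD, a shift of 3/7 of an SD, and a cut-off placed to give the control prevalence shown. Then p₂ = 1 − Φ(Φ⁻¹(1 − p₁) + 3/7). Power uses the usual two-proportion formula; each pair of figures is for pooled and unpooled variance. The prevalences of 28.9%, 49% and 74% are background figures in the Introduction. The 61% is an assumption, close to the midpoint of 49% and 74% (61.5%).

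| Metric | Power, 90 per arm, no design effect | Power, design effect 1.89 |
|---|---|---|
| Mean score, 3 points, SD 7 | 82% | 55% |
| 28.9% to 16.2% | 53–54% | 31–32% |
| 49% to 33% | 62–63% | 37–38% |
| 61% to 44% | 63–64% | 38–39% |
| 74% to 58% | 60–61% | 36–37% |

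Without a design effect, 80% power for the dichotomised shift would need about 136 to 170 per arm over these prevalences.

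**The case against.** The strongest reply is that the word proportions is a slip. The only quantified statement of the primary effect is a difference in mean score with an SD, and the omnibus F test also points to a mean-score analysis. No section defines the endpoint as a proportion. The model sentence in the Data Analysis Plan is generic: it covers one primary and six secondary outcomes, and a full protocol or analysis plan may map each outcome to its model. Most of this stands. It makes the mean score the likely intention, but it does not remove the contradiction inside the sample-size paragraph, which is an error of statement and not an omission.

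Three stronger readings are tempting, and the documents do not support them.

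- A reader might infer that the trial treats its primary endpoint as both a mean and a proportion. It does not. The proportion reading comes only from the formula wording, together with a logistic option that is attached to no named outcome.
- A reader might take the Introduction's percentages as proof that a yes/no definition swings with the cut-off. One survey has "three-quarters (74%) of adolescent girls and young women, and nearly half (49%) of adolescent boys and young men reported depressive symptoms", while other research gives 27.5% and 28.9%. These figures differ in sex, year and what was counted, and neither cut-off is given. They serve above only as illustrative prevalences.
- A reader might infer that the sponsor means to choose the metric after seeing the data, with an inflated false-positive rate. Nothing shows such intent, the analyst is to be blinded to allocation, and the calculations here concern power and not type I error.

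It is also fair to say that 82% is not the plan's own power, since the paragraph claims a design-effect adjustment. That is why both columns are shown.

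**Conclusion.** The point holds as a contradiction in the sample-size paragraph that the rest of the article leaves unresolved. The stated inputs are of a type that fits only a mean-score endpoint. Even on that reading, 90 per group does not follow once the stated intraclass correlation is applied to clusters of 90: the formula gives about 163 per arm, or about 55% power at 90.

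The contrast between metrics, 82% against 53% to 64% without a design effect and 55% against 31% to 39% with it, is illustrative. It rests on normal scores, a pure shift of 3 points, two-sided 5% and assumed control prevalences. The ordering does not depend on the design effect. The wording needs correcting and the metric needs confirming; nothing here shows that the intended analysis is wrong.

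**What to change.** 1. In Primary Outcome, name the PHQ-9 total score at one stated time point, 8 or 16 weeks.
2. In Data Analysis Plan, assign that outcome to the linear mixed model with a between-arm mean difference.
3. In Sample Size and Power Analysis, replace the reference to proportions with the formula for means, and restate the size or the power with the design effect actually applied and the cluster size it uses.
4. Label any above-cut-off analysis secondary, with one cut-off fixed before any unblinded outcome analysis. This must include the 8-week data: the Results section reports that the first follow-up survey was done in August 2022, so a deadline tied to the final survey would come too late.
5. If a binary primary endpoint was intended, state the cut-off and both rates and redo the sizing.

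If a fuller protocol or analysis plan already fixed the metric before outcome data were examined, citing it with its date meets items 1 and 2. Items 1, 2 and 4 cost a few sentences in the protocol and the registry entry. Item 3 needs a short recalculation, and its result may have to be reported as lower power, because enrolment and the first follow-up are complete. No new data are needed.

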### Data Collection and Management

Data will be collected using a structured survey on cell phones or tablets in all study languages by trained research assistants using the SurveyCTO app (Dobility), a secure platform that automatically encrypts data, which will be uploaded using a Secure Sockets Layer (SSL) certificate to a password-protected server. SurveyCTO allows for offline data collection, facilitates multilingual data collection, and has branching logic and consistency checks. To enhance confidentiality, all participants will be assigned a unique participant ID and no personal identifying information will be collected. Only study staff will have access to the data set on a need-to-know basis for the purpose of data management and outcome reporting. All data sets will be saved on a password-protected server.

### Data Analysis Plan

Analysis and reporting for the cRCT (Phase 2) will be conducted in accordance with CONSORT (Consolidated Standards of Reporting Trials) guidelines [59] (Multimedia Appendix 1). The analyst will be blinded to group allocation. A flow diagram will be used to illustrate patient flow (screening, randomization, allocation, follow-up). Baseline data will be reported for all three groups and summarized as mean (SD) or median (IQR) for continuous variables, and as counts and number (%) for categorical variables. The primary analysis will be intention-to-treat analysis (data from participants will be analyzed according to their allocation, irrespective of whether they actually received that intervention).

We will perform multivariable regression analyses, adjusting for the outcome measure at baseline and stratification variables. For the primary analysis to assess differences among the three intervention conditions on the outcomes, indicator variables will include intervention assignment and a vector of baseline covariates (eg, sociodemographics). Analyses will adjust for multiple comparisons across the three intervention conditions using the Fisher protected least-significant difference test, first assessing differences between intervention groups and, if the Omnibus *F* test is significant, subsequently calculating pairwise comparisons.

Between-group comparisons will be performed using multilevel mixed-effects logistic or linear regression models (to account for clustering) depending on which outcome is being evaluated. For these models, the intervention group will be entered as a fixed effect. The significance level will be set at α=.05. The results will be expressed as odds ratios or mean differences, as appropriate, accompanied by 95% CIs and *P* values. We will perform an adjusted analysis for the primary outcomes to investigate the role of various covariates on the relative effect. Covariates (eg, age) will be entered as a block. We will explore gender differences in primary and secondary intervention outcomes. Given that the outcomes of this study are related to behavior change and the trial is of a short duration with minimal risks, a data monitoring committee was not deemed necessary.

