## Discussion

### Projected Significance

Trial findings will generate novel evidence on promising low-cost mental health interventions delivered by and for refugee and displaced youth. Specifically, we anticipate finding that VR and GPM+ conducted on their own are feasible and will each be associated with improved mental health outcomes in comparison with standard of care. We also anticipate finding that when conducted in tandem, VR and GPM+ will be associated with greater improvements in mental health compared to when they are conducted separately and when compared with the standard of care. Importantly, the findings will enhance understanding of how VR interventions, effective in supporting adult mental health in high-income contexts [26], could be effective among urban refugee youth in LMICs. Study findings will also advance knowledge of how the WHO GPM+, effective with adults [30,31], could potentially benefit adolescents aged 16 years and older [27]. In sum, the findings will build on the limited evidence base of interventions to improve refugee youth mental well-being [3].

By measuring the effectiveness and feasibility of these novel, low-cost mental health innovations, this study has the potential to inform research, policy, and practice in the health, education, and social development sectors. Community partners and knowledge users will be involved in all stages of trial design, conduct, analysis, and dissemination. Findings regarding the effectiveness of GPM+ or VR in supporting mental health outcomes of refugee and displaced youth can inform the scale-up of such mental health interventions for other refugee youth in Uganda—both urban- and refugee settlement–based—as well as other urban forcibly displaced youth in East Africa.

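### The stated 80% power ignores the omnibus F gate; when 3 points is the largest difference between arms, gated power at 90 per arm is about 72% to 78% before clustering

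*Protocol article*

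**What the plan says.** Sample Size and Power Analysis in the protocol article states: "Cluster sizes of 90 per group (n=270) are required to have 80% power", for "a difference of ~3 points in mean depression score (moderate effect size", "at a level of significance of α=.05" and "assuming an intraclass correlation of 0.01 and SD of 7". It then allows for loss ("With 10% attrition, 297 participants (99 per cluster) are required") and sets the enrolment target ("The study aims to include 330 participants, with 110 per study arm"). It attributes the calculation to multiple-comparison formulae for proportions with a design-effect adjustment. It does not say which two arms differ by 3 points, where the third arm lies, or which test the 80% describes.

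The Data Analysis Plan adjusts for multiplicity "using the Fisher protected least-significant difference test, first assessing differences between intervention groups" and goes on to pairwise comparisons only if the omnibus F test is significant. The same section adjusts the models for the baseline value of the outcome.

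Projected Significance gives the expected order. VR alone should beat standard of care, and "when conducted in tandem, VR and GPM+ will be associated with greater improvements in mental health compared to when they are conducted separately". No sizes are attached.

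**The concern.** Under the declared procedure a 3-point difference between two arms is reported as significant only if both the three-group F test and the pairwise test pass. The power of that sequence cannot exceed the power of the pairwise test alone. How far it falls below depends on the third arm: the F test is weakest when that arm sits midway between the other two.

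The expected order is compatible with that pattern, with VR alone lying between control and the combination. If the 3 points is the combination against control, the stated 80% overstates what the planned tests can do. The figure matters when a null result is interpreted, because a reader would take 80% as the sensitivity of the procedure that was run.

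**Working it through.** **Inputs.** Difference 3, SD 7, alpha 0.05, ICC 0.01, 90 per arm, 10% attrition and 110 enrolled per arm, all from Sample Size and Power Analysis. The sidedness of the test is not stated; two-sided is assumed.

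**1. Reproducing the stated figure.**
- Ungated two-arm comparison, no design effect: n = 2 × 7² × (1.960 + 0.842)² / 3² = 85.5, so 86 per arm.
- Power at 90: standard error 7 × √(2/90) = 1.043; 3/1.043 = 2.875; Φ(2.875 − 1.960) = 82%.
- Detectable difference at 80% power with 90 per arm: 2.802 × 1.043 = 2.92, which is about 3.
- Other routes are further from 90: one-sided 68; Bonferroni 104 (two comparisons) or 114 (three); omnibus F alone 80 (third arm equal to one of the pair) or 106 (third arm midway).
- With the plan's ICC and 90 per site, the design effect is 1 + 89 × 0.01 = 1.89. Then 86 × 1.89 = 162.5, so 163 per arm.

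No route gives exactly 90 from all the stated inputs. The closest is the ungated pairwise test without a design effect.

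**2. Omnibus test at 90 per arm, no clustering.** Noncentral F on (2, 267) degrees of freedom, with λ = n × Σ(μᵢ − μ̄)² / 49.
- Means 0, 1.5, 3: the sum of squares is 4.5, λ = 90 × 4.5/49 = 8.27, power 73%.
- Means 0, 0, 3: the sum of squares is 6, λ = 90 × 6/49 = 11.02, power 85%.

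**3. Passing both tests.** 400,000 simulated trials per setting, pooled variance, 3n − 3 degrees of freedom. Two arms have means 0 and 3 and the third arm is moved. A trial counts if F is significant and the LSD t test for the 3-point pair is significant. Clustering enters only by multiplying the variance of each arm mean by the design effect.

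| Analysed per arm | Design effect | Ungated | Third arm halfway | Equal to one of the pair | 1 point outside the pair |
|---|---|---|---|---|---|
| 90 | none | 82% | 72% | 78% | 81% |
| 99 (110 × 0.9) | none | 85% | 76% | 82% | 85% |
| 110 | none | 89% | 81% | 86% | 88% |
| 90 | 1.89 | 55% | 42% | 47% | 52% |

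In the last row the gated figure rises to 54% with the third arm 2 points outside the pair, and reaches the ungated 55% at 3 points outside. Without clustering, 80% gated power needs about 108 analysed per arm with the third arm halfway, and about 95 with it equal to one of the pair.

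**The case against.** A reader might infer that the plan states power for an ungated pairwise test and that its procedure can never deliver 80%. The document supports neither claim. The sample-size section names no procedure beyond multiple-comparison formulae, and 90 cannot be rebuilt exactly from its inputs, so the ungated reading is an inference from the closest fit.

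A reader might also infer that the expected order fixes the least favourable case. It gives an order without sizes. If the 3 points is VR against control and the combination is at least 1 point better still, the order holds equally and, without clustering, the gate costs 1 point or less (81% to 82%).

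Two features of the plan soften the loss. Enrolment of 110 leaves 99 after 10% attrition, and gated power ignoring clustering is then 76% to 82%. Baseline adjustment adds precision for which the calculation takes no credit. The document gives no correlation; assuming 0.3, gated power at 90 would be 76% to 82%, and assuming 0.5, 84% to 89%, again without clustering.

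It is also fair to say that Fisher's protected LSD is a valid choice for three groups, that results will carry 95% CIs, and that nothing in the document says a non-significant F would be read as proof of no effect.

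What remains is that a power figure and a testing procedure are both stated, and the first does not take account of the second. The gap exceeds rounding in patterns that fit the sponsor's own expectation.

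**Conclusion.** The point holds conditionally. The 80% at 90 per arm makes no allowance for the omnibus gate and cannot be interpreted for the declared procedure until the contrast is named. Whenever 3 points is the largest difference among the arms, gated power at 90 is below 80% even without clustering, by about 2 points (third arm equal to either extreme) to 8 points (halfway). When the third arm lies at least 1 point outside the pair, there is no material loss without clustering.

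The design effect is the larger problem: it takes ungated power from 82% to about 55%. The gate is a separate loss that would remain after that is corrected.

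These figures assume two-sided tests, equal variances and no gain from baseline adjustment. They treat clustering only through the design effect. That is optimistic if, as Study Setting and the abstract suggest, there is one site per arm, because no between-site degrees of freedom would then be left to test the arms.

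**What to change.** In Sample Size and Power Analysis:
- Name the two arms to which the 3 points refers and state where the third arm is assumed to lie.
- Restate power for the omnibus F followed by LSD as a range over the third arm's position, with the design effect applied. On the stated inputs at 90 per arm this is about 42% (halfway) to 54% (2 points outside the pair). Before any design effect it is about 72% (halfway) to 82% (well outside the pair).
- Say that the range takes no credit for baseline adjustment because no correlation is given, and that handling clustering only through the design effect is optimistic with one site per arm.

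The cost is a less favourable stated figure. No new participants or data are needed, and the test procedure itself can stay as it is.

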**Methods:**

A three-arm cluster randomized controlled trial will be implemented across five informal settlements grouped into three sites, based on proximity, and randomized in a 1:1:1 design. Approximately 330 adolescents (110 per cluster) are enrolled and will be followed for approximately 16 weeks. Data will be collected at three time points: baseline enrollment, 8 weeks following enrollment, and 16 weeks after enrollment. Primary (depression) and secondary outcomes (mental health literacy, attitudes toward mental help–seeking, adaptive coping, mental health stigma, mental well-being, level of functioning) will be evaluated.

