## Methods

### Study Design

To evaluate intervention effectiveness, we will conduct a cluster randomized controlled trial (cRCT), in which five informal settlements in Kampala will be randomized at a 1:1:1 ratio to one of the three study arms. Peer navigators, refugee youth living in the five informal settlements, are trained in research methods and ethics, and will enroll youth into the study following obtaining written informed consent. Youth will be assigned to the study arm corresponding to the informal settlement they live in. A cluster randomization approach was selected to mitigate challenges of experimental contamination, as youth living in slums and informal settlements have shared sociophysical environments [44], thus addressing internal validity threats, although we will collect individual-level outcome data. We will perform data collection at three time points: baseline enrollment, 8 weeks following implementation, and 16 weeks following implementation.

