### Study Setting

This trial is being conducted in the Ugandan capital of Kampala in five informal settlements, grouped into three sites based on geographic proximity (1: Kabalagala and Kansanga, 2: Katwe and Nsambya, and 3: Rubaga). These settlements were purposively chosen because: (1) they host many refugee and displaced persons in Kampala [45-48], largely from the DRC, Rwanda, and Burundi [49]; (2) these communities share similarities in socioeconomic status and living conditions, health care access, and languages; and (3) prior research noted a high prevalence of depressive symptoms among urban refugee youth in these communities [4,17]. Full details regarding the trial site geography and population have been described elsewhere [50].

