### Study Population and Eligibility Criteria

Approximately 330 youth (110 per cluster) aged 16-25 years will be enrolled into this study. Eligibility criteria for inclusion are: (1) currently living in one of the five selected informal settlements in Kampala (Kabalagala, Kansanga, Katwe, Nsambya, or Rubaga); (2) identifying as a refugee or displaced person, or having refugee or displaced parents; (3) aged 16-25 years; (4) owning or have daily access to a mobile phone; and (5) speaking French, English, Luganda, Kirundi, Kinyarwanda, or Swahili. Eligibility screening (via phone, in person, or WhatsApp) with interested participants will be conducted by trained peer navigators.

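### With three sites allocated to three arms, no mixed model can separate arm from site, so the planned CIs and P values hold only if there is no between-site variance

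*Protocol article*

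**What the plan says.** **Unit of randomisation.** The Abstract (Methods) has "five informal settlements grouped into three sites, based on proximity, and randomized in a 1:1:1 design". Study Setting lists the settlements as "grouped into three sites based on geographic proximity (1: Kabalagala and Kansanga, 2: Katwe and Nsambya, and 3: Rubaga", so the sites hold two, two and one settlements. Study Design words it differently: "five informal settlements in Kampala will be randomized at a 1:1:1 ratio to one of the three study arms". It adds: "Youth will be assigned to the study arm corresponding to the informal settlement they live in".

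**Number of clusters.** Study Population and Eligibility Criteria gives "Approximately 330 youth (110 per cluster". Sample Size and Power Analysis gives 110 per study arm, and uses cluster and group for the same set of participants.

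**Analysis.** The Data Analysis Plan says "Between-group comparisons will be performed using multilevel mixed-effects logistic or linear regression models (to account for clustering", with arm as a fixed effect, an omnibus F test gating the pairwise tests, adjustment for the baseline outcome, and 95% CIs and P values at a 5% level. It does not name the level of the random effect.

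**Limitations.** Strengths and Limitations gives loss to follow-up and the resulting missing data as the primary limitations. It does not say that arm and site coincide.

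**The concern.** A mixed model accounts for clustering by comparing variation between arms with variation between clusters inside the same arm. With one site per arm there is no such within-arm variation. Anything that makes one site differ from another is then indistinguishable from the intervention. Adjusting for baseline PHQ-9 reduces stable differences between sites, but not differences in how sites change over the 16 weeks.

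At stake is the primary result. A local event or trend in one part of Kampala could be reported as an effect of VR or of VR plus GPM+, with a P value suggesting that clustering had been dealt with.

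**Working it through.** **Inputs**
- Sites 3, arms 3, settlements 5: Abstract, Study Setting, Study Design.
- 330 youth, 110 per cluster, 110 per arm: eligibility and sample-size sections.
- ICC 0.01, SD 7, difference about 3 points, 10% attrition: Sample Size and Power Analysis.
- Completers per site: 110 × 0.90 = 99. (The plan's own 99 per cluster is an enrolment requirement; the numbers happen to agree.)

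**1. The plan's own figure.** Required n per group without clustering is 2 × 49 × (1.96 + 0.84)² / 9 = 85.5, so 86. The plan states 90 and says it is adjusted for design effect. With 90 per cluster the design effect at ICC 0.01 is 1 + 89 × 0.01 = 1.89, giving 86 × 1.89 = 163. A figure of 90 implies a design effect of only 90 / 85.5 = 1.05. I could not reproduce 90 from the stated inputs. That is a separate problem, but the stated sample size gives no sign that site-level variance was carried through.

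**2. Clusters per arm.** 330 / 110 = 3 clusters, and 3 clusters / 3 arms = 1. Residual cluster degrees of freedom: 3 − 3 = 0.

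**3. What the data can say about site variance.** In one simulated data set with one site per arm (90 per arm, residual variance fixed at 48.5), the REML log-likelihood was −655.897 at every between-site variance tried. The SE of an arm difference depended entirely on the value supplied:

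| Between-site variance | Log-likelihood | SE of arm difference |
|---|---|---|
| 0 | −655.897 | 1.04 |
| 0.49 (= 0.01 × 49) | −655.897 | 1.43 |
| 5 | −655.897 | 3.33 |

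The likelihood is flat, so the data cannot choose between these SEs.

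**4. Size of the error if site is ignored, at the plan's ICC.**
- Design effect: 1 + (99 − 1) × 0.01 = 1.98.
- SE of a difference, ignoring site: √(2 × 49 / 99) = 0.99, about 1.0 PHQ-9 points.
- SE with site variance: 0.99 × √1.98 = 1.40. Both SEs are before baseline adjustment.
- Pairwise type I error: 2 × [1 − Φ(1.96 / √1.98)] = 2 × [1 − Φ(1.393)] = 0.164.
- Omnibus type I error (chi-square, 2 df, critical value 5.991): exp[−5.991 / (2 × 1.98)] = 0.220.

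A simulation at ICC 0.01 with 90 per arm (10,000 runs) gave 0.159 and 0.208.

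**5. Sensitivity to the ICC (assumed values, 90 per arm).**
- ICC 0.005: design effect 1.445; 10% pairwise, 13% omnibus.
- ICC 0.001: design effect 1.089; 6% and 6%.

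**6. The five-settlement reading.** Five units over three arms can only split 2-2-1 or 3-1-1, so at least one arm is a single settlement. Degrees of freedom: 5 − 3 = 2, critical t = 4.30. At ICC 0.01 and 90 per arm, the SE is 1.25 (two settlements against two) or 1.35 (two against one), and power for 3 points is about 28% or 25%. If the variance sits at site level, a settlement random effect does not capture it: in simulation it still rejected about 12% of true nulls pairwise and 15% for the omnibus test.

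**The case against.** **The random-effect level may be set elsewhere.** This is true: the Data Analysis Plan names no site random intercept, and a reader should not infer one. Settlement, participant or group-session effects could be fitted. None of them separates site from arm, because the confounding comes from the allocation. It is therefore not a detail that a fuller analysis plan could settle.

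**The true inflation may be smaller.** This stands in part. Study Setting says the settlements were chosen partly for similar socioeconomic status, living conditions, health care access and languages, and baseline adjustment may lower the ICC. The 16% and 22% are conditional on ICC 0.01 and are not predictions. But 0.01 is the plan's own assumption, and validity at 5% needs zero.

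**Stronger readings that the documents do not support**
- That the fitted model would return a particular absurd SE. Software may report some value from a flat likelihood, but that reflects the optimiser and does not measure the plan's error.
- That the adjustment "adjusting for the outcome measure at baseline and stratification variables" must mean site and should be deleted. The article does not define these variables, and a fuller protocol may do so.
- That "thus addressing internal validity threats" claims protection from site confounding. In context it concerns contamination between youth who share surroundings, and for that the cluster design is reasonable.
- That inflating SEs at an assumed ICC would make the inference valid. It shows how much the result depends on the ICC, but leaves site and arm confounded.

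**Conclusion.** The point holds. On the description in the Abstract, Study Setting, eligibility and sample-size sections, there is one cluster per arm, and the stated mixed model cannot account for site-level clustering. Study Design contradicts those sections on the randomised unit, and its reading does not rescue the analysis.

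The planned CIs and P values are valid only if there is no between-site variance, including in change over time after baseline adjustment. At the plan's ICC of 0.01 with 99 completers per site, ignoring site gives about 16% type I error pairwise and 22% omnibus; at an assumed 0.005 with 90 per arm, about 10% and 13%. These figures assume two-sided testing at 5%, equal site sizes, normally distributed site effects, and an ICC that baseline adjustment does not change. The residual ICC is unknown and this trial cannot estimate it between sites.

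**What to change.** Baseline data, the intervention and the first follow-up are complete according to the Results section, so adding clusters is not realistic. The changes are to analysis and wording.

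1. State one unit of randomisation consistently in the Abstract, Study Design, Study Setting and eligibility sections.
2. In the Data Analysis Plan, stop stating that the mixed model accounts for site-level clustering. Say that arm and site coincide, and label the individual-level, baseline-adjusted CIs and P values as conditional on no site effect.
3. Beside these, report SEs and CIs inflated by √(1 + (m − 1) × ICC), at 0.01 and over a range fixed in advance. Present this as a sensitivity analysis, not as a correction.
4. In Strengths and Limitations, list the confounding of arm with site as a primary limitation. Describe effects as differences between three sites under different interventions. In Study Design, qualify the internal-validity statement as applying to contamination only.

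The cost is wider intervals and a weaker causal claim. At ICC 0.01 the 95% half-width before baseline adjustment grows from 1.96 × 0.99 = 1.9 to 1.96 × 1.40 = 2.7 points. If the range reached an assumed 0.05, the design effect would be 1 + 98 × 0.05 = 5.9, the SE 0.99 × √5.9 = 2.4, and the half-width about 4.7 points, which exceeds the 3-point target difference.
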